### **3.6 Recruitment of study participants**

A total of 150 children completing the study are needed. From our previous studies in children we expect a drop-out of up to 15-20%, and expect unsuccessful blood sampling in an additional 10% of the children at either baseline or endpoint. Therefore, a total of 200 participants will be recruited.

Boys and girls of the relevant age will be identified through the Danish Civil Registration System (CPR registry) and recruited via postal invitation letter to the parents (Appendix 2). Participants will mainly be recruited from the Capital Region of Denmark, but if necessary also from other parts of Zealand. Participants may also be recruited through advertisements in Danish newspapers, shared through networks and social media such as Facebook, and by notices in schools and after school clubs (Appendix 6). Parents that respond to the advertisements will receive the same information material as parents contacted through the CPR registry. The letter will contain a link to an electronic response form and the information material (Appendix 3). The brochure "The legal rights of study participants in a health science research project" [Forsøgspersonens rettigheder i et sundhedsvidenskabeligt forskningsprojekt], published by the Danish Committee on Biomedical Research Ethics system in August 2014, will be included in the information material.

Parents are asked to carefully read the material, if they wish together with a family member or a friend, and to explain the content to their child. Parents who return the response form will be called by telephone by the project staff. Here the participants will be pre-screened according to the inclusion and exclusion criteria. If they are still interested in participating, they will be invited to an information meeting where the study will be explained orally to parents and child by a project staff member who has been specifically trained for this task. Parents will be informed that they can bring an assessor (e.g. a family member or a friend) to the information meeting, if they wish so. If the participants do not fulfil the criteria for participation they will be informed hereof and will not be contacted or bothered further. Only one eligible child from each household can be included as a study participant, since for practical reasons individual randomization within a household is not possible.

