## **3. METHODS**

### **3.1 Study design**

The study has a block-randomized controlled 12-week parallel design (**Figure 1**). It will include two groups of 100 children each; one group that receives fatty fish and one group that receives poultry.

The study participants will be 8-9 year-old healthy Danish children who will be enrolled from summer 2016 to April 2017. Apart from an information meeting the study consists of a pre-visit, a baseline visit and an endpoint visit which will be held at Department of Nutrition, Exercise and Sports (NEXS), [name].

[figure not shown]

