## **5. STATISTICAL CONSIDERATIONS**

### **5.1 Statistical power**

The primary outcomes of the study will be diastolic blood pressure and plasma triacylglycerol. Power calculations were performed using data from our previously conducted OPUS School Meal Study (23). With 150 completing children we will have 80% power to detect a difference of less than 0.5 SD of the outcomes i.e. 2.7 mmHg in diastolic blood pressure and of 0.13 mmol/L in triacylglycerol between the two intervention groups, respectively. This would correspond to approximately 4% reduction in blood pressure and 20% reduction in plasma triacylglycerol among this age group, which is considered relevant and obtainable.

The cognitive measurements will be secondary and exploratory outcomes, and therefore not subject to power calculation. However, in the OPUS School Meal Study we previously found that school meals rich in fish improved school performance and reading comprehension in Danish 8-11 year-olds (52). Although the sample size was about 4 times larger in that study, the fish group of FiSK Junior will get 5-10 times more n-3 LCPUFA than in the school meal study, and therefore we expect FiSK Junior to have a sufficient sample size for the cognitive outcomes as well.

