### **5.2 Statistical analysis**

The effect of the intervention on the outcomes will be evaluated using analysis of covariance including baseline outcome values as covariate. Outcomes will also be analyzed with gender and genotype as potential effect modifiers.

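### Recruiting 200 children yields the 150 needed for triacylglycerol only at the 15% end of the protocol's own drop-out range, and a single n of 150 does not fit both primary outcomes (minor)

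*Protocol*

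**What the plan says.** Section 3.6 sets the requirement: "A total of 150 children completing the study are needed". On losses, the investigators "expect a drop-out of up to 15-20%, and expect unsuccessful blood sampling in an additional 10% of the children", where the failed sample may be the one at baseline or the one at endpoint. From these it concludes: "Therefore, a total of 200 participants will be recruited". Section 3.1 fixes the split: "It will include two groups of 100 children each".

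Section 5.1 rests the power statement for both primary outcomes, diastolic blood pressure and plasma triacylglycerol, on the same number: "With 150 completing children we will have 80% power to detect a difference of less than 0.5 SD of the outcomes". It translates this into 2.7 mmHg and 0.13 mmol/L. It gives no standard deviation, significance level, sidedness or baseline-endpoint correlation.

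Section 5.2 plans "analysis of covariance including baseline outcome values as covariate". Section 3.3 places allocation at the end of the baseline visit, after the baseline measurements.

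**The concern.** The conclusion in section 3.6 is presented as following from its inputs, but it covers only part of the attrition range given in the same paragraph. At the 20% end, the number of children with triacylglycerol at both visits drops below the 150 on which section 5.1 rests.

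The two primary outcomes also lose children for different reasons. Drop-out affects both, but a failed blood sample removes only triacylglycerol. One n for both understates the data for blood pressure and may overstate them for triacylglycerol.

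Finally, section 3.6 counts a failed sample at either visit as a lost child. A child whose baseline sample failed but who has an endpoint value still carries information on the treatment effect. At stake are an accurate size statement for one primary outcome and a little precision that could be recovered.

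**Working it through.** **Inputs.** From section 3.6: 200 recruited, 150 needed, drop-out up to 15-20%, failed sampling a further 10%. From section 3.1: equal groups. From section 5.1: 80% power at 150, 2.7 mmHg, 0.13 mmol/L. Assumed, because not stated: two-sided alpha of 5%.

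**Reproducing the plan's figures.** 150 / (1 − 0.15 − 0.10) = 200 exactly, so the target corresponds to the 15% end. With N children in two equal groups, the difference detectable with 80% power is (1.960 + 0.842) × √(4/N) SD. At N = 150 this is 0.457 SD (0.460 SD with the t distribution), which agrees with the protocol's claim of less than half an SD.

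**Children available out of 200.** The additional 10% can be read as 10% of those recruited (additive) or of those remaining (multiplicative).

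| | 15% drop-out | 20% drop-out |
|---|---|---|
| Diastolic blood pressure | 200 × 0.85 = 170 | 200 × 0.80 = 160 |
| Paired triacylglycerol, additive | 200 × 0.75 = 150 | 200 × 0.70 = 140 |
| Paired triacylglycerol, multiplicative | 200 × 0.85 × 0.90 = 153 | 200 × 0.80 × 0.90 = 144 |

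The shortfall at 20% is 6 to 10 children. Covering it by recruitment alone would take 150 / 0.72 = 208.3, so 209, or 150 / 0.70 = 214.3, so 215.

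**Effect on triacylglycerol.** Take 0.13 mmol/L as the 80%-power difference at 150 (0.4575 SD) in an unadjusted comparison. Power is Φ(0.4575 × √(N/4) − 1.960), and the detectable difference scales as 0.13 × √(150/N).

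| N | Detectable difference, SD (normal / t) | mmol/L | Power |
|---|---|---|---|
| 153 | 0.453 / 0.456 | 0.129 | 80.8% |
| 150 | 0.457 / 0.460 | 0.130 | 80.0% |
| 144 | 0.467 / 0.470 | 0.133 | 78.4% |
| 140 | 0.474 / 0.477 | 0.135 | 77.2% |

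**Sensitivity to what is not stated.**
- If 0.13 mmol/L is 0.5 SD, power at 140 is Φ(0.5 × √35 − 1.960) = Φ(0.998), or 84.1%.
- If the planning SD was unadjusted, adjusting for baseline multiplies it by √(1 − ρ²). Power returns to 80% when 1 − ρ² = N/150. That is ρ = √(1 − 140/150) = 0.26 at 140, or √(1 − 144/150) = 0.20 at 144.

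**Diastolic blood pressure.** On the same assumptions, with 2.7 mmHg as 0.4575 SD, power is Φ(0.4575 × √40 − 1.960) = 82.5% at 160 and Φ(0.4575 × √42.5 − 1.960) = 84.7% at 170.

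**Keeping children with a failed baseline sample.** Assume half of the 10% failures occur at baseline. Only the endpoint half then costs children: at 20% drop-out, 200 × (0.80 − 0.05) = 150 or 200 × 0.80 × 0.95 = 152.

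**The case against.** The drop-out is worded as an upper limit, and at 15% the target of 200 is sufficient. Read literally, section 3.6 asks for 150 children completing, and even 20% drop-out gives 160 completers. Both points stand, so a reader should not infer that 200 is too few in general. But section 3.6 includes failed sampling in the derivation of 200, and it names 20% as part of its expectation; that end is not covered.

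A reader might also infer that the stated 80% power is not met. The protocol does not support this. Its claim is 80% power for a difference below half an SD, and at 140 children the detectable difference is still 0.474-0.477 SD. The loss to 77-78% applies only to 0.13 mmol/L under the assumptions above, and other readings of the protocol leave power at or above 80%.

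A third inference would be that the planned analysis of covariance discards children without a baseline value. Section 5.2 does not say so, and a statistical analysis plan commonly settles missing data, so its absence here is no fault. What stands is narrower: section 3.6 itself counts baseline failures as losses when it derives the sample size, and that loss is avoidable.

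**Conclusion.** The point holds as a minor one. The target of 200 covers 15% drop-out plus 10% failed sampling, but not 20% plus 10%, where 140-144 children have paired triacylglycerol values against the 150 in section 5.1. Diastolic blood pressure keeps 160-170. These counts need only the protocol's own figures.

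The cost in power is 2-3 percentage points for triacylglycerol, or 0.003-0.005 mmol/L in the detectable difference. It arises only at the unfavourable end of the range, and only with two-sided 5% alpha, an unadjusted comparison and 0.13 mmol/L as the 80%-power difference at 150. Because the SD, alpha and baseline correlation are not given, the protocol cannot settle whether power for 0.13 mmol/L would fall below 80% at all. Nothing here biases the comparison.

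**What to change.** 1. Restate sections 3.6 and 5.1 by outcome over the full attrition range: 160-170 children for diastolic blood pressure and 140-153 for paired triacylglycerol. Give the matching power and detectable difference, and the alpha, SD and any baseline correlation used. More children need not be enrolled.
2. Keep every randomised child with an endpoint triacylglycerol value in the primary analysis of covariance. Handle a failed baseline sample by mean imputation with a missing-indicator, or by a baseline-constrained longitudinal model. The baseline sample is taken before allocation, so its failure cannot depend on the assigned group, and retaining these children does not bias the randomised comparison.
3. Make the n stated under (1) match the analysis chosen under (2). If these children are retained, the triacylglycerol figure at 20% drop-out becomes about 150-152, on the assumption that half the failures are at baseline.

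The cost is some rewording, slightly more analysis work and, if only paired values are counted, a slightly less favourable stated figure for triacylglycerol.

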### **3.7 Information meeting**

Information meetings will be held individually or in groups of max. 10 families in a dedicated room by one or more project staff members. At this meeting the parts of the study that involves the family and child will be explained in detail and there will be time and room for asking questions. Parents will be informed that they and the potential assessor can ask questions to a project staff member, who has been delegated for this task in a separate room one to one. If the project staff judges that some parents need a second explanation of the study, this will be encouraged. It will be emphasized that the participants have the right to consideration time of at least 24 hours, that participation is voluntary, and that the participants can withdraw from the study at any time without giving a reason.

In case they want to participate and do not wish further consideration time, both parents/custody holders can fill out the consent form for the child and for being invited for potential future follow-ups of the study (Appendix 4a) and for the biobank (Appendix 4b), if they wish to allow storage of possible excess material of blood in the biobank. Consent to donate biological material for the biobank and consent to allow us to contact the families in relation to future follow-ups of the study are not required for participation. The project staff will explain the content of the consent forms to the parents. If the parents give written consent to be invited for potential future follow-up of the study, they will only be invited after the potential follow-up study has been approved through a supplementary protocol submission to the Danish Regional Committee on Biomedical Research Ethics.

When both parents or all custody holders of the child as well as the project responsible (or a project staff member who have had this responsibility assigned by the project responsible) have signed the consent form(s), parents are offered a copy of the signed form(s). One parent or custody holder can empower by signature the other parent/ custody holder to decide whether the child should participate (Appendix 5). There will not be conducted any project activities before written informed consent has been given.

### **3.8 Under age study participants**

The study participants are under age. We consider the study to be substantiated according to Committee Regulations [Komitelovens § 19, stk. 3] regarding trials not involving drugs, since the study can only be conducted in the described age group in order to answer the relevant research questions. Also, the study confers minimal risk of harm for the participants.

According to Committee Regulations [Komitelovens § 5, stk. 2] the information to the study participant needs to be suited for the apprehension of the participant, and information to under age participants has to be given by a person with understanding of the area of study and relevant pedagogical skills for the age group. At the information meeting the study and study activities will be explained to the child in a language and at a level that is appropriate and suited for the age and apprehension of the child, and with use of visual images if required, by a project staff member with experience in communicating to children.

As the study participants are under age they cannot give informed consent. However, the project staff informing and talking with the child will be aware of the child's response. If the project staff judges that the child does not want to participate in the study, the child will not be included.

### **3.9 Study activities**

The different elements of the study are listed in **Table 1**. During the study we will send the parents reminders by text message and/or email; this procedure will be described at the information

meeting. We will make sure to plan the 4-5 hour visits at NEXS with appropriate breaks for the child including time for breakfast that will be provided to the child.

**Table 1. Elements of study activities**

|                                                 |                                                                                                                                                                                                                                                                                                                                                                                                                                                                                                                                                                                                                                                                                                                                                                                                                                                     |
|-------------------------------------------------|-----------------------------------------------------------------------------------------------------------------------------------------------------------------------------------------------------------------------------------------------------------------------------------------------------------------------------------------------------------------------------------------------------------------------------------------------------------------------------------------------------------------------------------------------------------------------------------------------------------------------------------------------------------------------------------------------------------------------------------------------------------------------------------------------------------------------------------------------------|
| Information meeting at NEXS
(1 hour) | 
 
• An understandable presentation of the context and purpose of the study
 
• Explanation of the study procedures and measurements.
 
• Any foreseeable risks, side effects, complications and inconveniences
 
• Unpredictable risks
 
• The right for time to reflection
 
• Volunteering
 
• Confidentiality
 
• The right to decline information on the study results
 
• That all data collected during the study will be used in the event of a participant chooses to withdraw from the study
 
• Description of the study products/food
 
• Review of the pamphlet "Before you decide" published by DNVK August 2014
 
• Questions from the parents
 
• Explanation of informed consent and withdrawal
 
 |
| Pre-visit at NEXS
(1 hour)           | 
 
• Informed consent
 
• Inclusion/exclusion criteria
 
• Instructions on 4-day dietary recording
 
• Instructions on accelerometer measurements
 
• Cognitive pre-testing
 
                                                                                                                                                                                                                                                                                                                                                                                                                                                                                                                                                                                              |
| At home before baseline visit            | 
 
• Fill out lifestyle questionnaire (Appendix 7)
 
• Fill out questionnaire on puberty
 
• Fill out questionnaire(s) on behavior, emotions, and cognitive function (Appendix 9-11)
 
• 4 days of dietary recording
 
• 7 days + 8 nights of physical activity and sleep recording (accelerometer)
 
• Apply EMLA patches to the child's forearms
 
• Overnight fasting
 
                                                                                                                                                                                                                                                                                                                                                                                   |
| Baseline visit (4-5 hours)               | 
 
• Empty bladder if possible
 
                                                                                                                                                                                                                                                                                                                                                                                                                                                                                                                                                                                                                                                                                                                                                                       |
| Cardiovascular function                         | 
 
• Blood pressure and heart rate
 
• Continuously measured heart rate by electrocardiograms
 
                                                                                                                                                                                                                                                                                                                                                                                                                                                                                                                                                                                                                                                                                                 |
| Anthropometric measurements                     | 
 
• Height
 
• Weight
 
• Waist circumference
 
• Body composition
 
                                                                                                                                                                                                                                                                                                                                                                                                                                                                                                                                                                                                                                                                                                             |
| Biological samples                              | 
 
• Hair strands
 
                                                                                                                                                                                                                                                                                                                                                                                                                                                                                                                                                                                                                                                                                                                                                                                    |

|                                           |                                                                                                                                                                                                                                                                                                                                                                                                                   |
|-------------------------------------------|-------------------------------------------------------------------------------------------------------------------------------------------------------------------------------------------------------------------------------------------------------------------------------------------------------------------------------------------------------------------------------------------------------------------|
|                                           | 
 
• Blood sample
 
• Salivary samples
 
                                                                                                                                                                                                                                                                                                                      |
| Other                                     | 
 
• Child has breakfast
 
                                                                                                                                                                                                                                                                                                                                           |
| Cognitive function, behavior and emotions | 
 
• Tests, interviews and questionnaires
 
                                                                                                                                                                                                                                                                                                                          |
| Study foods                               | 
 
• Interview on dietary habits, preferences, and perceptions
 
• Instructions on intake and recording of study foods
 
• Receive first batch of study foods
 
                                                                                                                                                                                        |
| During the intervention (12 weeks) | 
 
• Collect study foods from NEXS (every 1-2 weeks)
 
• Cook and eat study foods
 
• Register intake of study foods
 
                                                                                                                                                                                                                                 |
| At home before endpoint visit      | 
 
• Fill out lifestyle questionnaire (Appendix 8)
 
• Fill out questionnaire on behavior, emotions, and cognitive function (Appendix 9-11)
 
• 4 days of dietary recording
 
• 7 days + 8 nights of physical activity and sleep recording (accelerometer)
 
• Apply EMLA patches to the child's forearms
 
• Overnight fasting
 
 |
| Endpoint visit (4-5 hours)         | 
 
• Empty bladder if possible
 
                                                                                                                                                                                                                                                                                                                                     |
| Cardiovascular function                   | 
 
• Blood pressure and heart rate
 
• Continuously measured heart rate by electrocardiograms
 
                                                                                                                                                                                                                                                               |
| Anthropometric measurements               | 
 
• Height
 
• Weight
 
• Waist circumference
 
• Body composition
 
                                                                                                                                                                                                                                                                           |
| Biological samples                        | 
 
• Hair strands
 
• Blood sample
 
• Salivary samples
 
                                                                                                                                                                                                                                                                                              |
| Other                                     | 
 
• Breakfast
 
                                                                                                                                                                                                                                                                                                                                                     |
| Cognitive function, behavior and emotions | 
 
• Tests, interviews and questionnaires
 
                                                                                                                                                                                                                                                                                                                          |
| Study foods                               | 
 
• Interview on dietary habits, preferences, and perceptions
 
                                                                                                                                                                                                                                                                                                     |

